### Recruitment

The study will continue until the minimum of 192 valid observations are collected in every arm. As part of the antenatal cardiology consult, women with will be offered a short meeting with a member of the recruitment team. During this appointment, they will be offered participation in the trial. To increase participant enrolment a second patient screen will be carried out by medical staff during admission to the Neonatal Intensive Care Unit. The enrolment period will extend over 36 months. Recruitment rates will be monitored monthly. In return, women will be offered additional breastfeeding support.

### Assignment of interventions

#### Allocation (sequence generation, concealment mechanism and implementation)

A member of the recruitment team will approach caregivers within the infant's first 72 h of life. He or she will explain the study and obtain written consent for participating in the trail. Infants who fulfill inclusion criteria will be randomized.

A study number together with the allocated treatment will be assigned by REDCap. The allocation sequence will be computer-generated. Patient's data along with the result of the allocation will be sent to statistical team. Block randomization with stratification by type of lesion (ductal dependent pulmonary, systematic, or mixing blood flow) will be implemented. Patients will be randomly assigned to standard or physician-led enteral nutrition guidelines in 1:1 ratio. To ensure allocation concealment, the randomization list will remain with the statistical team for the whole duration of the study. The block size will be variable and concealed until primary endpoint analyses.

Thus, randomization will be conducted without any influence of the principal investigators, clinicians, recruitment or follow up staff.

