**Data collection**								
Baseline demographics	x							
VIS	x	x	x	x				
Protein and caloric intake	x	x	x	x				
days on mechanical ventilation	x	x	x	x				
CLABSI		x	x	x				

CLABSI, central line associated blood stream infection; VIS, vasoactive inotropic support score.

This study is designed as a randomized, parallel-group, superiority multi-center trial, with an 1:1 allocation and stratification by type of lesion.

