### Methods: Participants, interventions, and outcomes

#### Study setting

The study will be carried out in four neonatal centers in Poland, including two neonatal departments at the Medical University of Warsaw (MUW), and one Neonatal Unit at Children's Health Memorial Institute (CHMI), and Polish Mother's Memorial Hospital (PMMH).

Departments of Neonatology at MUW are level III and IV teaching hospitals with approximately 5,000 (150 CHD) deliveries per year. Both units are referral centers for fetuses with CHD. Having access to high-risk mothers will augment recruitment. CHMI and PMMH are regional level IV hospital providing neonatal, cardiac, and surgical care for infants with CHD. A certified breastfeeding consultant is available daily on each unit.

The local feeding regimes for infants with CHD are set at the discretion of the attending doctor. However, the staff, in both units, is willing to implement new procedures to improve neonatal outcome.

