1. A bowel wall thickness of >2, 7 mm accompanied by an increase in echogenicity will be considered as suspicious. Color Doppler (CD) ultrasound will be required to evaluate blood flow in the superior mesenteric artery (SMA), and bowel wall perfusion (BWP). Evaluation of BWP; three categories of flow in the bowel wall will be recognized in color Doppler: *normal* (1–9 CD signal dots per cm^2^), *increased* (“zebra” pattern, “Y” pattern or “ring” pattern), and *absent* (when no color Doppler signals will be present) which will be reported as transmural necrosis.2. Bowel wall thickness below 1.0 mm will be considered as abnormal thinning because of ischaemia or necrosis. Measurements will be recorded in relaxed bowel segments.3. PI will be defined as small intramural hyperechoic focuses in the bowel wall, which will not change position despite peristalsis, respiratory movement, or abdominal compression with the transducer.4. Abnormal peristaltic contractions of the small bowel will be defined as <10 movements/min.5. For evaluation of PVG, the portal vein will be adjusted in a transverse or longitudinal section of the liver. PVG will be defined as highly echogenic round particles with a diameter of approximately 1 mm registered within portal circulation.6. Using a transverse section of the right upper abdomen showing the liver just below the diaphragm, free abdominal gas will be detected as a bright echogenicity between the abdominal wall and the anterior surface of the liver.7. Free abdominal fluid will be evaluated as an hypoechogenic material between the bowel loops.

To assess the SMA flow the transducer will be held in the longitudinal section just below the xiphoid. Elevated systolic velocities (up to100–120 cm/s), and high diastolic velocity will be suspicious for NEC.

Ultrasonographer experience will vary between centers (5 to 20 years of experience). All examinations will be performed at the bedside and saved on a secure web-based platform. No specific pre-test requirements will be required.

Plain AR using a vertical and horizontal beam will be repeated every 12–24 h as the disease tends to progress rapidly (42). The following plain abdominal radiography findings will be considered typical for NEC:

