### Statistical methods

#### Statistical methods for primary and secondary outcomes

As the trial is designed as a superiority study, both primary and secondary outcomes will be analyzed based on the per-protocol (PP) approach.

For primary outcomes and dichotomous secondary outcomes, between-group differences, and the two-sided 95% confidence interval (CI) for the estimated difference approach will be used (47–49).

For continuous outcomes, means/medians and 95% CIs will be calculated. Differences in changes from baseline between treatment groups will be compared using a two-sample t test or Mann-Whitney *U*-test (50).

Additionally, a predictive model to clarify the risk of NEC complications in both study groups will be implemented. Statistical and machine learning techniques such as decision trees, random forests, and support vector machine (SVM) will be used (51–55).

All statistical calculation will be carried out using R package (The R Foundation Vienna, Austria) and Statsoft (Hamburg, Germany).

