#### Interim analyses

Our study is a multicentre study, located in 4 different unit. Three interim analyses (IA) will be performed on the primary end point every 100 recruited patients. IA will be conducted by an independent statistician, blinded for the treatment allocation. This will allow us to track trial data collected on case report forms and generate performance metrics. Additionally, it will make data and study information available in a timely manner and re-estimate the sample size if needed. Results of interim analyses will be reported to the DMC, which will decide whether the trial should be continued or stopped for futility based on the pre-specified criteria. The Peto approach will be used: the trial will be ended using symmetric stopping boundaries at *P* < 0.001 (56).

Additionally, sensitivity analysis for the primary outcomes will be carried out with an intention-to-treat (ITT) approach. Protocol deviations will be reviewed by a blinded adjudication DMC who will decide by consensus whether a patient should be included in the ITT or per protocol population. We do not plan any subgroup analyses. In case of missing data, standard data imputation algorithms will be used (e.g., multiple imputation) (55).

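### Centre is not a stratification factor and does not appear in the primary analysis as described: a small loss of precision in a four-centre trial, cheap to recover

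*Protocol article*

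**What the plan says.** - **Centres.** Study setting: "The study will be carried out in four neonatal centers in Poland". Two are university departments that act as referral units for affected fetuses; two are regional hospitals with cardiac and surgical care.
- **Randomisation.** Trial design describes a parallel-group trial "with an 1:1 allocation and stratification by type of lesion". The Allocation section repeats this: "Block randomization with stratification by type of lesion (ductal dependent pulmonary, systematic, or mixing blood flow) will be implemented". Block sizes are variable and concealed. Centre is not named in either place.
- **Analysis.** For the primary outcomes, Statistical methods states: "between-group differences, and the two-sided 95% confidence interval (CI) for the estimated difference approach will be used". Continuous outcomes are compared by a two-sample t test or Mann-Whitney U test. Neither description has a term for centre or lesion type. The Interim analyses section adds: "We do not plan any subgroup analyses".
- **What could vary by centre.** Under the data-collection plan for the primary outcome: "Ultrasonographer experience will vary between centers (5 to 20 years of experience". Study setting says of feeding: "The local feeding regimes for infants with CHD are set at the discretion of the attending doctor". The text after the exclusion criteria says in general terms that practice is not the same across units and physicians.

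**The concern.** NEC may be diagnosed by ultrasound or by plain radiograph, and several of the ultrasound signs (wall thickness, perfusion, peristalsis, mesenteric flow) depend on the operator. The comparator is discretionary feeding. It is therefore plausible, though not shown, that the observed NEC rate differs between centres.

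If it does, centre predicts the primary outcome. With one allocation list per lesion type shared by all sites, a centre with a high NEC rate can by chance supply more infants to one arm. An unadjusted comparison leaves that chance difference in the estimate and leaves between-centre variance in the standard error. What is at stake is precision and the face credibility of the comparison.

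**Working it through.** **Inputs from the protocol.** NEC 18% (control) and 7.6% (intervention), difference 10.4 points; 80% power, 5% significance; 192 per arm, 384 in total; four centres; 1:1 allocation.

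**Inputs assumed, because the protocol gives none.** Equal centre sizes; blocks of 4 or 6; lesion mix 35/40/25%; no effect of lesion type on NEC; control NEC rates by centre as listed below; a common odds ratio of (0.076/0.924)/(0.18/0.82) = 0.37.

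**1. The plan's own figure.** The two-sided pooled formula at 80% power gives 161 evaluable infants per arm (unpooled 159). Multiplied by 1.2 these are about 193 and 191, so 192 corresponds to 160 × 1.2. The point below does not depend on this figure.

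**2. Standard error of the planned difference.**
√[(0.18 × 0.82 + 0.076 × 0.924)/192] = √(0.2178/192) = 0.034, or 3.4 points.

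**3. Shift caused by chance centre imbalance.** SD of shift ≈ SD of the centre rates × √(2/n per arm). The share of outcome variance due to centre is var(p)/[p̄(1 − p̄)].

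| Assumed control NEC rates by centre | SD of rates (points) | SD of shift at 192 per arm | Variance share |
|---|---|---|---|
| 18% in all four | 0 | 0 | 0 |
| 10/15/21/26% | √36.5 = 6.0 | 6.0 × 0.102 = 0.6 points | 36.5/(18 × 82) = 2.5% |
| 7/12/20/33% | √96.5 = 9.8 | 9.8 × 0.102 = 1.0 point | 96.5/(18 × 82) = 6.5% |

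For a narrower spread of 10–16%, the variance share is about 0.4%.

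**4. Simulation.** 384 infants, blocks within lesion type only, 3,000 runs per scenario; unadjusted z-test against a Cochran-Mantel-Haenszel test stratified by centre.

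| Assumed rates | Power, unadjusted | Power, by centre | 95th percentile of absolute shift |
|---|---|---|---|
| 18% in all four | 88.3% | 87.9% | 0 |
| 10/15/21/26% | 86.5% | 87.1% | 1.2 points |
| 7/12/20/33% | 85.2% | 87.2% | about 2 points |

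Type I error was 4.6 to 5.3% unadjusted and 4.7 to 5.3% by centre. The mean shift was zero throughout. The simulated powers carry a Monte Carlo error of about √(0.87 × 0.13/3000) = 0.6 points, so the small loss with equal rates is within noise.

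**5. Interim looks.** At 200 infants the shift has SD 6.0 × √(2/100) = 0.85 points (second scenario) and the standard error is √(0.2178/100) = 4.7 points, a ratio of 0.18. At 384 infants the ratio is 0.62/3.37 = 0.18. Both quantities scale with 1/√n, so the relative effect is the same at every look.

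**The case against.** The strongest reply has four parts.

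- **Randomisation already deals with this.** Individual 1:1 allocation gives centre imbalance a mean of zero, and the unadjusted standard error includes between-centre variance. This stands. A reader might infer that the NEC comparison is biased; the type I error in the simulation shows that it is not.
- **The centre differences are largely inferred.** This also stands. A reader might take case-mix and ultrasound reading to be documented as different. The protocol describes unit roles, not case-mix, and lesion type is already stratified. It reports years of sonographer experience, not reading results, and sets common diagnostic criteria. It describes feeding variation at the trial sites mainly as variation between staff, which centre strata would not remove; the remark about units is general.
- **Uneven splits look alarming early.** With equal centres and the overall total held at 1:1, a 60:40 or worse split in at least one centre has probability about 0.41 at 200 infants and 0.09 at 384. A reader might infer that the problem is worst at the interim looks. A split is not an effect on the NEC difference, though, and step 5 of the working shows that its weight relative to the standard error does not change.
- **The design choice is defensible and the SAP is not shown.** In an open-label trial, a list shared across sites makes the next allocation harder to guess. Transfers are expected, so the enrolling centre need not be where NEC is detected. Covariate adjustment is often left to the SAP, so its absence can be stated only of the analysis this article describes.

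What survives is narrow: the stated strata omit centre, the stated analysis is unadjusted, and the protocol itself gives a reason to expect some variation between centres.

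**Conclusion.** The point holds as a minor one about efficiency. With lesion-only stratification and an unadjusted comparison, the trial gives up about 0 to 2 points of power and leaves a chance shift with SD 0.6 to 1.0 point (95th percentile 1.2 to 2.0) in an estimate whose standard error is 3.4 points. Those figures rest on assumed control NEC rates by centre of 10–26% to 7–33% and on equal centre sizes. If the rates are close, the gain is negligible. The simulation adjusts for centre only and gives lesion type no effect, so any gain from adjusting for lesion type is not counted. Validity is not in question.

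**What to change.** **Analysis, the main change.** Unless the SAP already does so, estimate the NEC risk difference stratified by lesion type and centre with Mantel-Haenszel weights, and include both factors as covariates in a regression for continuous outcomes. This gives one overall estimate and is not a subgroup analysis, so it is compatible with the decision not to run any. Centre is known for every infant, so the cost is a line in the plan, written before unblinded data are seen. With 4 × 3 = 12 strata of about 384/12 = 32 infants and an average NEC rate of (18 + 7.6)/2 = 12.8%, each stratum would hold about four events; Mantel-Haenszel weighting is suited to strata that sparse.

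**Randomisation, secondary.** Only if randomisation has not started, add enrolling centre as a second factor in REDCap, keeping the variable concealed blocks. The cost is a new list, more incomplete blocks and slightly greater predictability within a site in an open-label trial. If recruitment is under way, make the analysis change alone.

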### Blinding (masking)

Assessments regarding the clinical course will be conducted by an assessor blind to treatment allocation. Due to the nature of the intervention staff cannot be blinded to allocation but are strongly inculcated not to disclose the allocation status of the participant at the follow up assessments. A member of the research team blinded to treatment allocation will feed data into REDCap.

### Data collection and management

#### Plans for assessment and collection of outcomes

All baseline data will be collected based on electronic MN.

#### Primary outcome

Patients will be evaluated for NEC based on the presence of at least three of the following clinical symptoms (37–40).

Abdominal distention.Visible bowels loops.Feeding intolerance (defined as emesis ≥2 consecutive feeds, or gastric residuals of >50% per feed in ≥2 consecutive feeds, bilious residuals, bilious emesis).Temperature instability (defined as ≥2 consecutive measurements).Frank bloody stools.Cardiovascular instability (hypotension; defined as MAP <30 mmHg, tachycardia >160/' or bradycardia <80/').Recurrent apnoea.Increase of abdominal girth > 2 cm (allowing inter-observer variability of 1 cm) within 12 hAbdominal wall erythema.

And/or at least 2 of the below laboratory findings based on Walsh and Bell criteria (modified by Kliegman) (25, 37).

Thrombocytopenia < 50 kLeukopenia <6 kCRP > 10 mg/dlPCT > 1 IU/lCoagulopathy.

NEC will be diagnosed using the abdominal ultrasonography (AUS) or plain abdominal radiography (AR).

Gray- scale AUS will be used to assess bowel wall echogenicity, measure bowel wall thickness, peristalsis, pneumatosis intestinalis (PI), portal vein gas (PVG), free abdominal air and fluid. The following finding on AUS will be equivalent do NEC (41):

1. A bowel wall thickness of >2, 7 mm accompanied by an increase in echogenicity will be considered as suspicious. Color Doppler (CD) ultrasound will be required to evaluate blood flow in the superior mesenteric artery (SMA), and bowel wall perfusion (BWP). Evaluation of BWP; three categories of flow in the bowel wall will be recognized in color Doppler: *normal* (1–9 CD signal dots per cm^2^), *increased* (“zebra” pattern, “Y” pattern or “ring” pattern), and *absent* (when no color Doppler signals will be present) which will be reported as transmural necrosis.2. Bowel wall thickness below 1.0 mm will be considered as abnormal thinning because of ischaemia or necrosis. Measurements will be recorded in relaxed bowel segments.3. PI will be defined as small intramural hyperechoic focuses in the bowel wall, which will not change position despite peristalsis, respiratory movement, or abdominal compression with the transducer.4. Abnormal peristaltic contractions of the small bowel will be defined as <10 movements/min.5. For evaluation of PVG, the portal vein will be adjusted in a transverse or longitudinal section of the liver. PVG will be defined as highly echogenic round particles with a diameter of approximately 1 mm registered within portal circulation.6. Using a transverse section of the right upper abdomen showing the liver just below the diaphragm, free abdominal gas will be detected as a bright echogenicity between the abdominal wall and the anterior surface of the liver.7. Free abdominal fluid will be evaluated as an hypoechogenic material between the bowel loops.

To assess the SMA flow the transducer will be held in the longitudinal section just below the xiphoid. Elevated systolic velocities (up to100–120 cm/s), and high diastolic velocity will be suspicious for NEC.

Ultrasonographer experience will vary between centers (5 to 20 years of experience). All examinations will be performed at the bedside and saved on a secure web-based platform. No specific pre-test requirements will be required.

Plain AR using a vertical and horizontal beam will be repeated every 12–24 h as the disease tends to progress rapidly (42). The following plain abdominal radiography findings will be considered typical for NEC:

PI is most commonly present in the distal small bowel and large bowel, hence it is usually seen in the right lower quadrant, although it may be present in any part of the gastrointestinal tract (43, 44).PVG as an extension of intramural gas present in bowel wall veins, passing into the portal vein system (28, 29).*Free intraperitoneal gas* as a result of bowel perforation, which usually is in the distal ileum and proximal colon. It is the only universally accepted radiologic indication for surgical intervention (12).

We will define *AUS as positive for NEC* when three of the following findings are appreciated on examination (41):

1. Abnormal bowel wall thickness (<1.0 mm or >2,7 mm)2. PI3. Free abdominal fluid as a focal fluid collection4. Abnormal SMA blood flow, or bowel wall perfusion.

And one of the listed findings:

1. Free abdominal air2. Delayed peristalsis3. PVG.

AR will be classified *as positive for NEC*, if one of the following findings will be present (23):

Intramural gas (pneumatosis intestinalis)Portal venous gasFree intraperitoneal gas

*And*

Bowel dilatation.

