### Criteria for modifying or discontinuing allocated interventions

In infants who present with *one or two* of the following symptoms such abdominal distention, visible bowels loops or feeding intolerance (defined as emesis ≥2 consecutive feeds, or gastric residuals of >50% per feed in ≥2 consecutive feeds, bilious residuals, bilious emesis) the intervention will be **modified** by decreasing enteral nutrition by 50% and substituting the remaining fluid requirements with adequate parenteral nutrition for a **maximum** of 48 h. If symptoms persist above 48 h, the trial will be discontinued.

The trial will be **discontinued** if the following occur:

The patient presents with at least three of the following symptoms.

Abdominal distention.Visible bowels loops.Feeding intolerance (defined as emesis ≥2 consecutive feeds, or gastric residuals of >50% per feed in ≥2 consecutive feeds, bilious residuals, bilious emesis)..Temperature instability (defined as ≥2 consecutive measurements).Presence of bowel perforation of NEC confirmed on abdominal x-ray or ultrasound.

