### Outcomes

#### Primary outcomes

##### Necrotizing enterocolitis and death related to NEC

The primary outcomes will include Stage II or III of NEC as defined by Kliegman and Walsh (25) and death related to NEC.

Stage II NEC will be defined as distended abdomen and radiological symptoms (intramural and/or portal gas). Stage III NEC will be defined as distended abdomen, radiological symptoms (intramural and/or portal gas) and respiratory and cardiovascular failure requiring mechanical ventilation and inotropic support (25). In surgery verified cases no radiological verification will be required.

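### The imaging rules under Data collection do not match the gas criterion that defines the primary endpoint under Outcomes, and the article does not say which governs

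*Protocol article*

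**What the plan says.** The protocol article deals with the NEC endpoint in two places.

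- **Outcomes, Necrotizing enterocolitis and death related to NEC.** The endpoint is Stage II or III NEC and NEC-related death. "Stage II NEC will be defined as distended abdomen and radiological symptoms (intramural and/or portal gas"). Stage III keeps the same radiological criterion and adds respiratory and cardiovascular failure. There is one waiver: "In surgery verified cases no radiological verification will be required".
- **Data collection and management, Primary outcome.** This section starts with nine clinical signs ("Patients will be evaluated for NEC based on the presence of at least three of the following clinical symptoms") and five laboratory findings ("And/or at least 2 of the below laboratory findings based on Walsh and Bell criteria"). It then says that NEC is diagnosed by abdominal ultrasound or plain radiograph, and it defines a positive result for each:
  - Ultrasound is positive "when three of the following findings are appreciated on examination" (abnormal wall thickness, pneumatosis, focal free fluid, abnormal mesenteric flow or wall perfusion) together with one of free air, delayed peristalsis or portal vein gas.
  - A radiograph is positive "if one of the following findings will be present" (intramural, portal venous or free intraperitoneal gas) together with bowel dilatation.

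Neither section refers to the other, and neither is given precedence.

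**The concern.** Both sections define something that decides who has a primary endpoint event. One does so by the presence of intramural or portal gas. The other uses combinations of findings in which that gas is neither sufficient nor, for some combinations, necessary. The same images from the same infant can therefore be a case under one stated rule and not under the other.

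Four centres will classify cases, and the same endpoint feeds three interim analyses. If the choice between the rules is left open, it will be made by each reader or centre, or at analysis. A primary endpoint in a trial with few events should not carry that discretion.

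**Working it through.** **1. The two criteria side by side**

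| | Outcomes section | Data collection section |
|---|---|---|
| Distension | required | not part of either imaging rule |
| Intramural or portal gas | required unless surgically verified | not sufficient on either modality, and not always necessary |
| Bowel dilatation | not mentioned | required on radiograph |
| Free intraperitoneal gas | not listed | accepted on radiograph with dilatation; second-list item on ultrasound |
| Wall thickness, fluid, flow, peristalsis | not mentioned | can make an ultrasound positive without gas |

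**2. Ultrasound rule**

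Treat the seven findings as present or absent, and read the thresholds as at least three and at least one.

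- All patterns: 2^7 = 128.
- Positive: (at least 3 of 4) × (at least 1 of 3) = 5 × 7 = 35.
- Neither intramural nor portal gas: 2^5 = 32, so 128 − 32 = 96 contain at least one of them.
- Positive without either gas: thickness, fluid and flow must all be abnormal (1 way), with free air, delayed peristalsis or both (3 ways). That is 1 × 3 = 3.
- Positive with gas: 35 − 3 = 32. Negative with gas: 96 − 32 = 64.
- Both gases present: 32 patterns. The result is negative if at most one of thickness, fluid and flow is abnormal (4 of 8 ways), whatever the free air and peristalsis (4 ways). That is 4 × 4 = 16.

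Example, gas but negative: pneumatosis and portal gas with normal wall, no focal fluid and normal flow. Example, positive but no gas: abnormal wall thickness, focal fluid, abnormal flow and delayed peristalsis.

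**3. Radiograph rule**

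Four findings: intramural, portal and free gas, and dilatation.

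- All patterns: 2^4 = 16.
- Positive: (at least 1 of 3 gases) × dilatation = 7 × 1 = 7.
- Intramural or portal gas present: 3 × 2 × 2 = 12. Half of these, 6, lack dilatation and are negative.
- Positive with neither of those gases: free gas plus dilatation, 1 pattern.

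The rules therefore disagree in both directions on both modalities.

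**4. What one infant weighs**

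The Sample size section gives rates of 18% and 7.6%, 80% power, 5% significance, and 192 per arm with 20% loss. The unpooled two-sided formula gives 7.849 × (0.18 × 0.82 + 0.076 × 0.924) / 0.104² = 158.07, so 159 per arm, and 159 × 1.2 = 190.8, so 191. The pooled formula gives 161, and 161 × 1.2 = 193.2, so 194. The plan's 192 lies between them, so it already includes the allowance, and 192 / 1.2 = 160 are left per arm.

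Expected events are 160 × (0.18 + 0.076) = 41.0, or 192 × 0.256 = 49.2 with no loss. One infant classified differently is then 1/41.0 = 2.4% or 1/49.2 = 2.0% of all events.

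**The case against.** **The sections are steps in sequence.** Signs and laboratory findings prompt the work-up, imaging is read, and the Outcomes section then stages the disease. For the sign and laboratory lists this is the better reading. A reader might infer that three signs are a further threshold for the endpoint, in conflict with the single sign of distension under Outcomes. The text does not support that: it speaks of evaluating patients and then gives the diagnosis to imaging. The sequence does not reconcile the imaging rules themselves. An image called negative for NEC may show exactly the gas that defines Stage II.

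**Positive for NEC need not mean Stage II.** A gas-free positive ultrasound could be a positive image without being an endpoint case. That is possible, but the rules stand under the heading Primary outcome and the article does not draw the distinction.

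**Either modality suffices, and radiographs are repeated every 12–24 hours.** This stands in part. The pattern counts are per modality, and an infant negative on ultrasound may be positive on radiograph. An infant with gas, no dilatation and fewer than three first-list ultrasound findings stays negative on both.

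**The surgical waiver covers free gas.** Largely so, because the article treats free gas as an indication for surgery. It does not cover gas-free ultrasound positives without an operation, or gas-positive infants called negative.

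**Fuller documents may settle it.** They may add detail, but both rules are stated here, so one of them would have to be overruled.

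**Conclusion.** The point holds as an inconsistency between two stated imaging criteria for the primary endpoint. It rests on the text alone and on reading the ultrasound thresholds as minimum counts.

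Its size in infants is unknown. A reader might take 64 of 96 to mean that two thirds of gas-positive ultrasounds would be missed. The enumeration gives every pattern equal weight, and real findings cluster, so it shows that disagreement is possible and not how often it occurs. A reader might also infer lost power or bias between the arms. The article gives no sensitivity or specificity for either rule, and the same rules apply in both arms, so neither inference is supported. What can be said is that each infant classified differently would be about 2% of the 41 to 49 events expected at the plan's rates.

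It should be corrected, because the ambiguity concerns the primary endpoint and is cheap to remove.

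**What to change.** 1. In the Primary outcome section under Data collection and management, state that the Outcomes definition determines the primary endpoint in both arms, and that the sign and laboratory lists are prompts for imaging, not preconditions for diagnosis.
2. State that intramural or portal gas seen on either ultrasound or radiograph meets the radiological criterion, without requiring bowel dilatation or other ultrasound findings.
3. State explicitly whether a gas-free positive ultrasound, or free intraperitoneal gas without intramural or portal gas, counts. The default consistent with the present Outcomes text is that it counts only if verified at surgery. If the investigators want it to count otherwise, that is a clinical choice, and the finding should be added to the Outcomes definition.
4. Record distension, each gas finding, its modality and any surgical verification as separate items on the case report form, so that the rule can be applied identically at every centre.

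The cost is a wording amendment and a case-report-form change. Sample size and visit schedule are unaffected.
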